## Abstract

**Background:**

Physical activity during childhood and adolescence is associated with substantial health benefits and tracks into adulthood. Nevertheless, only 22.7% of German adolescents are sufficiently physically active. Thus, the promotion of an active lifestyle in youth is an essential issue of public health.

This study will evaluate the implementation and efficacy of the “läuft.” program to enhance physical activity in adolescence. “läuft.” is a multicomponent school-based program developed on the basis of effective strategies for health interventions and behavioral change.

**Methods/design:**

The “läuft.” physical activity program targets four different levels. (a) Each student receives a pedometer and documents his/her steps over 12 weeks using an interactive user account on the “läuft.” homepage. (b) For classes there will be different competitions, with achieving the most steps in selected weeks, the highest increases of steps and developing the most inventive ideas to promote physical activity in school. Besides, the intervention includes four educational lessons. (c) The headmasters and teaching staff of the participating schools will get information material with suggestions and encouragement to enhance physical activity in school. Participating teachers will be invited to an introductory seminar. (d) Parents will be provided with informational material about the program and will be invited to a parent-teacher conference about the benefits of being physically active and how they can support their children in engaging in a physically active lifestyle.

To evaluate the efficacy of the “läuft.” physical activity program, a two-arm cluster randomized controlled trial will be conducted in three waves: (1) baseline assessment, January/February 2014, (2) post assessment, June/July 2014 and (3) 12-month follow-up assessment, June/July 2015. Data collection will include physical and medical testing, self-administered questionnaires, group discussions and document analyses.

**Discussion:**

“läuft.” aims at fostering a physically active lifestyle in adolescence while a considerable decline of physical activity is present. Physical activity programs based in the school setting and following a multicomponent approach have been proven to be most successful. Furthermore, the use of pedometers is promising to enhance physical activity during the entire day and targets a wide range of adolescents regarding fitness and weight.

**Trial registration:**

Current Controlled Trials ISRCTN49482118.

## Background

There is extensive literature emphasizing physical activity as an important and modifiable factor influencing physical and mental health: being physically active on a regular basis is associated with substantial health benefits [1-4], including primary and secondary prevention of chronic diseases, a reduced risk of premature death and better mental health.

Physical activity in childhood and adolescence prevents a widespread variety of chronic diseases, including hypertension, obesity and depression [5,6]. An active lifestyle early in life is not just important for health outcomes in adolescence but may also be a significant factor for the level of activity in adulthood and health-related physical fitness [7-10]. Global recommendations on physical activity suggest that children and adolescents should take part in physical activity of moderate to vigorous intensity for at least 60 minutes per day to maintain health [11]. In consideration of epidemiological data, only 17.3% of female and 28.2% of male adolescents in Germany aged 11 to 17 years meet these recommendations [12]. Moreover, physical activity declines in older adolescents compared to children and younger adolescents [13]. Nader *et al*. reported a decline of moderate-to-vigorous physical activity from 180 minutes per day at 9 years to only 42 minutes per day at 15 years [14]. Hence, the promotion of an active lifestyle and physical fitness in early adolescence is an issue worthy of intervention development.

Considering the access to a large adolescent population, interventions based in the school setting are supposed to be the method of choice for increasing physical activity in youth [15]. Meta-analyses and reviews indicated positive impacts of school-based interventions for promoting physical activity on health-related indicators, namely an increase of rate and duration of in-school physical activity as well as aerobic fitness and a decrease of blood cholesterol and of physical inactivity [15-18]. Notably, multicomponent interventions involving peers, parents and communities were assumed to be highly effective [18]. However, despite these encouraging outcomes, almost no improvements in out-of-school physical activity has emerged from studies to date, and increases in activity level were rather short-term [17,18]. Therefore, school-based programs which aim to enhance physical activity and fitness in adolescents should also focus on changing the everyday routine to increase out-of-school physical activity and on establishing an active lifestyle in the long term.

There are several options for interventions to induce effects on physical activity throughout the entire day. One promising approach could be the use of pedometers which has already been shown to be effective in increasing physical activity among adolescents [19,20], not just in-school but also during out-of-school [21,22]. These findings are supplemented by studies emphasizing self-monitoring and goal-setting as one of the most effective intervention strategies to promote physical activity [23,24]. Both strategies can be easily and effectively combined with pedometer use [20]. The “läuft.” program integrates these strategies that have been proven to be successful in the promotion of physical activity into a multicomponent approach [15,18] that is school-based [15,17,18] and includes social support from peers and parents [25], goal-setting and self-monitoring through pedometer use [23,24].

### Objectives and hypotheses

The aim of the study is to evaluate the implementation and effectiveness of the “läuft.” physical activity program among adolescents in grade 8. Therefore, a two-arm three-wave cluster randomized controlled trial will be conducted. Expected effects on primary outcomes of the “läuft.” program in the intervention compared to the control group are defined as:

1. an increase in physical activity in general and in different contexts measured by questionnaires;

2. a decrease of sedentary behavior measured by questionnaires; and

3. an increase in cardiovascular fitness measured by the 20-meter shuttle run test.

In addition to primary outcomes, the following secondary outcomes will be included in the evaluation study of the “läuft.” physical activity program: body composition (that is, Body Mass Index (BMI), percentage of body fat mass and waist circumference), cardiovascular risk factors (that is, blood pressure, heart rate after stress as well as resting and recovery heart rate), mental health (that is, general self-efficacy, psychological well-being, self-esteem and depression), enjoyment of physical activity and sedentary behaviors, physical self-concept (that is, general physical capacity and physical attractiveness), self-efficacy towards physical activity, intention for physical activity and physical well-being.

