### Study design

The effectiveness of the “läuft.” physical activity program will be tested in a two-arm three-wave cluster randomized controlled trial. Data of the different waves are hypothesized to be clustered at the individual, class and school level. Schools are the units of randomization and will be randomly allocated to the intervention and control group. In intervention schools the “läuft.” physical activity program will be implemented, while schools of the control group run through the usual curriculum and will receive no further intervention. In both groups, fitness, medical and questionnaire data will be collected for three times: “baseline” (immediately before the intervention), “post” (immediately after the intervention) and “follow-up” (12 months after the end of the intervention) assessment. In addition, after the intervention, qualitative analyses will be conducted in classes of the intervention group to gain insight into interactive processes within the classes and to reconstruct subjective experiences and interpretations of activating-strategies.

Process evaluation of the planned trial will be realized through questionnaires and interviews during and after the study, respectively. The study design is presented in Figure 2.

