### Sample size calculation

There are specific constraints for analysis of cluster randomized trials [26] since the responses of individuals within a cluster tend to be more similar than those of individuals of different clusters. This clustering effect can be defined as 1 + (m-1)p, where m is the average number of subjects per cluster and p the intraclass correlation coefficient (ICC) [27]. The ICC for physical fitness and adiposity was taken from another cluster randomized controlled trial, the Kindersportstudie (KISS) [28,29] and estimated with approximately 0.05 (p). Assuming an equal average cluster size of 20 pupils with parental consent (m = 20), a clustering effect of 1.95 was determined. Without taking into account the clustering of the data, assuming a small to medium effect size of the intervention (Cohen’s d = 0.30) on physical activity as one primary and the most important outcome being still detectable at follow-up, applying a significance level of alpha = 0.05 and power = 0.80, it can be estimated that N = 350 pupils are required to detect a difference between two independent sample means [30,31]. Taking the cluster effect into account, a required sample size of N = 683 students and 34 classes was determined. A computerized sample size calculator for cluster randomized trials was used to confirm this estimation [32].

Based on earlier experiences [33,34], a drop-out rate of 25% over the study was hypothesized. Hence, a total sample size of 911 pupils and 46 classes will be recruited for baseline to detect possible differences between the groups at follow-up. In order to recruit the estimated sample size of 46 classes while assuming a participation rate of 20% and an average of at least two participating classes per school, about 100 schools will be invited to participate.

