##### Lifestyle behavior

Adapted items of the MoMo-activity-questionnaire [38] will be used to assess physical activity in different contexts (school, sports clubs and leisure time) and in different dimensions (duration, frequency and intensity) as well as the mode of commuting to school. These questions provide information about physical activity during a regular week. Besides, students in the pilot study were asked with which activities they choose to spend their recess time in school. The three activities that were named the most (sitting or standing while talking to others, walking through the school or schoolyard, and sports such as football or basketball) will be included in the final questionnaire. Students will be asked how often they engaged in these activities during the recess times of the last week. Overall moderate to vigorous physical activity will be determined by a reliable and validated two-item screening measure [39]. The survey method for leisure time sedentary behavior was modified from Zabinski and colleagues [40]. Students will be asked how much time they spent on the most recent school day and the most recent Sunday with different sedentary behaviors. Different physical activities were added to the list providing insights into the distribution of sedentary and active leisure time during a specific day. The list of activities is based on the original questionnaire, categories for physical activity (active transport, household activities, physical activity in sports clubs, in school and in leisure time), and extended by answers of students in the pilot study. Lifetime smoking and current smoking [41] as well as lifetime alcohol use, current alcohol use and frequency/number of previous binge drinking [42,43] will be assessed. Finally, students will be asked how often they consume different foodstuff in a usual week, namely, fresh fruits and vegetables, sweets or chocolate, soft drinks, fast food and water [44] (retest-reliability (r) ranged from 0.39 to 0.63).

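### Three outcomes are declared primary, one of them an open family of activity measures, without saying which measure, wave or success rule carries the efficacy claim, while the sample size covers a single test

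*Protocol article*

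**What the plan says.** All references are to the protocol article.

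- **Objectives and hypotheses** gives three numbered primary outcomes: "an increase in physical activity in general and in different contexts measured by questionnaires", "a decrease of sedentary behavior measured by questionnaires" and "an increase in cardiovascular fitness measured by the 20-meter shuttle run test". It ties none of them to a wave, and it does not say whether one, some or all must succeed.
- **Lifestyle behavior** shows how wide the first outcome is. "Overall moderate to vigorous physical activity will be determined by a reliable and validated two-item screening measure". Separate questionnaire items cover activity at school, in clubs and in leisure time, each by duration, frequency and intensity, as well as the way of getting to school and what pupils do at recess.
- **Study design** states that "fitness, medical and questionnaire data will be collected for three times": at baseline, directly after the intervention, and 12 months after its end. Two waves could therefore show an effect.
- **Sample size calculation** rests on "physical activity as one primary and the most important outcome being still detectable at follow-up". It sets alpha at 0.05 and power at 0.80, and this is the only place where an alpha level is given.
- **Statistical analysis** plans a multilevel model with schools, classes, individuals and waves as levels. It does not say which wave contrast is the primary test.

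**The concern.** The sample size describes a trial with one main question: does physical activity differ at follow-up? The objectives describe a trial with at least three, the first of which can be answered by several instruments. The two sections do not fit together.

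Until the carrying measure and wave are named, an efficacy claim could rest on whichever outcome, context or wave looks favorable once the data are in. Its false-positive risk would then exceed the level used for the sample size. A statistical analysis plan may properly hold the multiplicity procedure. Which outcome, measure and time point are primary is a protocol decision, and the objectives make it in a form that leaves the claim open.

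**Working it through.** **1. The plan's own figure.** Inputs from Sample size calculation: d = 0.30, alpha = 0.05, power = 0.80, ICC 0.05, 20 pupils per cluster, 25% drop-out.

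- Per arm: 2 × (1.960 + 0.842)² / 0.30² = 174.4, rounded up to 175, so N = 350. This matches. Sidedness is not stated, but a one-sided test would give 276, so the plan's figure is two-sided.
- Clustering: 1 + 19 × 0.05 = 1.95; 350 × 1.95 = 682.5, so 683.
- Drop-out: 683 / 0.75 = 910.7, so 911.

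The figures are right for one two-sided test at 0.05.

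**2. Error rate if any one success counts.** Assumptions, not in the article: each test is two-sided at 0.05, and one significant result is enough. For k independent tests the chance of at least one false positive is 1 − 0.95^k. If only errors in favor of the program count, it is 1 − 0.975^k. For correlated tests I simulated equicorrelated normal test statistics (1,000,000 draws).

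| Tests | Correlation | Any false positive | Favoring the program only |
|---|---|---|---|
| 1 | – | 5.0% | 2.5% |
| 3 (three outcomes, one wave) | 0 | 1 − 0.95³ = 14.3% | 1 − 0.975³ = 7.3% |
| 3 | 0.5 | 12.5% | 6.3% |
| 3 | 0.7 | 10.9% | 5.5% |
| 6 (three outcomes, two waves) | 0 | 1 − 0.95⁶ = 26.5% | 1 − 0.975⁶ = 14.1% |
| 6 | 0.5 | 20.8% | 10.4% |
| 6 | 0.7 | 16.5% | 8.2% |

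Testing each activity context separately would raise these figures further. The article fixes no number of such tests, so I attach no figure to that case.

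**3. Error rate if all three outcomes must succeed.** The risk would not exceed 5%. The article does not state this rule either.

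**4. What splitting alpha would require.** Bonferroni over three outcomes at one wave gives 0.05 / 3 = 0.0167 per test. To keep 80% power at d = 0.30:

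- unclustered: 466
- clustered: 466 × 1.95 = 908.7, so 909
- recruited: 909 / 0.75 = 1,212

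With the planned 350 effective pupils, power per outcome would fall from 80% to 66%.

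**The case against.** The strongest reply is that much of this is silence, and that a journal article may leave the success rule, the multiplicity procedure and the wave contrast to a fuller document. That stands for the procedure, and I do not count its absence as an error. It does not cover the objectives, which do choose the primary outcomes and choose them as an open list.

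Second, a partial hierarchy exists. The sample size section ranks physical activity first and powers it at follow-up. This also stands, and it reduces the problem. But that section still calls activity only one of the primaries and picks no measure within the family, and the objectives carry over neither the ranking nor the wave.

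Third, the hypotheses are directional, so two-sided error rates overstate the risk of a wrong claim for the program. That is fair, and the table's last column answers it. For three outcomes at one wave the favorable-only risk is 5–7%, which is two to three times the nominal 2.5%.

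A reader might also infer that every outcome will be tested at both waves at 0.05 each, or might count every activity item and recall day as its own primary test and reach an error rate of one half or more. The article does not support either reading. Alpha is stated only for the sample size of one outcome at follow-up, the analysis section sets no wave-specific tests, and no passage makes the context items, recess items or recall days separate primary endpoints.

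**Conclusion.** The point holds as a mismatch between the objectives and the sample size. The objectives declare three primary outcomes, the first a family, with no carrying measure, wave or success rule. The sample size covers one two-sided 0.05 test of physical activity at follow-up.

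The size is conditional. If any one success counts at 0.05, the chance of at least one false positive is about 11–14% for three outcomes at one wave and about 16–27% for three outcomes at two waves. Counting only errors favoring the program, the ranges are about 5–7% and 8–14%, against 2.5%. They rest on an assumed any-success rule, an assumed number of tests, and an assumed correlation between 0.7 and 0. Under an all-must-succeed rule there would be no inflation. What does not depend on these assumptions is that the article leaves open which result would count as evidence of efficacy. This should be corrected; it does not invalidate the design.

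**What to change.** In Objectives and hypotheses and in Statistical analysis:

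1. Name one primary endpoint that agrees with the sample size section: overall moderate-to-vigorous physical activity from the two-item screener, compared between groups at the 12-month follow-up, two-sided 0.05.
2. If that test is significant, test sedentary behavior and then shuttle-run fitness at follow-up, in that fixed order, each at two-sided 0.05.
3. Report context-specific activity and all results of the post wave as secondary.

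Alpha stays at 0.05 and the sample size at 683 (911 recruited). A Bonferroni split over the three outcomes would instead need 1,212 recruited pupils, or leave 66% power per outcome at the planned size.

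The cost is mainly in wording. The real loss is that sedentary behavior, fitness and context-specific activity no longer have stand-alone primary status: if the activity test fails, no confirmatory claim can be made for sedentary behavior or fitness. Out-of-school activity is one of the program's stated motives, so the context results should still be reported in full, but as secondary evidence. The Trial status section says recruitment had not begun at submission, so at that stage only the text had to change.

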## Methods/design

### Intervention

“läuft.” was designed by an interdisciplinary team of sport medicine specialists, sport scientists, teachers, nutritional scientists and psychologists.

The intervention operates at four levels: individual, class, school and parents. The intervention period is 12 weeks. An overview of all components of the intervention is shown in Figure 1.

**Figure 1 F1:**
[figure not shown]
Overview of intervention components.

#### Class

The core components of the intervention are class competitions. On the one hand, each individual student in the class receives a pedometer and records the daily amount of steps over a period of 12 weeks. Steps are summed up to a class mean, documented on a class poster and reported to the project staff in three selected weeks. On the other hand, each class collects creative and inventive ideas on how to increase physical activity in everyday school life and keeps records of these ideas on the “läuft.” homepage (http://www.laeuft.info). In addition, the classes take part in four educational lessons: (1) introduction to the “läuft.” program, distribution of pedometers and informational material for students and their parents, (2) introduction to the creativity contest, (3) physical activity that combines running/walking with exercises at environmental facilities (for example, a bench, stairs or a jungle gym), and (4) reflection of strategies to take more steps in everyday life and setting of physical activity goals for the time period after the project. Besides, additional modules are offered that can be flexibly conducted during the program. The modules deal with topics such as the reflection of student’s physical activity, motives for being physically active or possible barriers to physical activity and how to handle them. Each lesson takes 45 minutes and will be conducted by teachers of the participating classes. After the end of the competition period, classes with the highest means of steps per week, with the largest increases and with the most inventive and creative class projects are awarded.

#### Individual

By using a pedometer, each student can evaluate his or her daily physical activity objectively and compare it to the class mean and common recommendations. Additionally, students can document their steps as well as their experiences during the program using a private and interactive user account on the “läuft.” homepage. Based on students’ entries, statistics (for example, mean of the week or day of best performance), a diagram to follow daily step totals over time and feedback will be delivered. Furthermore, the homepage provides opportunities to share experiences with other participating students and compete on step totals. The homepage is optimized for online use with smartphones.

#### School

The headmaster and entire teaching staff of each participating school will receive information material, including background and description of the program, activity-promoting teaching methods, suggestions on how to improve the school environment to stimulate physical activity, and related links leading to further information. All participating teachers will be offered an introductory seminar to learn more about the concept and components of the “läuft.” program.

